### Ethical approval and informed consent

This study has been approved by the Ethics Committee of Clinical Trials, Affiliated Hospital of Southwest Medical University, with the approved number: KY2020001. Participants who sign up will be screened, for those who meet the inclusion criteria, we will issue informed consent to them, and inform them in detail of the study purpose and process, number of participants, study duration, potential risks and benefits, random allocation, and data confidentiality.

## Discussion

In developed countries, the focus of AIDS prevention education is on the sexual behavior of high-risk groups, but the focus of AIDS education in our study is on the AIDS-related knowledge of adolescents. The awareness rate of AIDS knowledge among the public in developed countries might be higher than China, and existing studies are mainly aimed at high-risk groups, such as men who have sex with men and adolescents who have sex without condoms [18, 19]. But in China, the awareness rate of AIDS among the public is low [20], especially adolescents in poor areas and western China [21, 22].

Adolescents are in the sexually active period are a high-risk group of HIV infection [23], the awareness rate of AIDS among them is low [24], and the HIV infection rate is high in China [25], AIDS preventive education for them is crucial. Therefore, the target of HIV prevention education in China should be the public, especially adolescents.

To meet the need of AIDS education of adolescents, the educational game “AIDS Fighter · Health Defense” was developed. As mentioned above, AIDS Fighter · Health Defense is a theory-based AIDS education game that can provide knowledge and skills to adolescents to prevent AIDS. Whether adolescents are interested in AIDS Fighter · Health Defense and insist on using it is the key to this study. If the game does not appeal to adolescents, it will not be popularized among them, nor have educational significance. To promote the use of this game by adolescents, the game is designed to be highly interactive and interesting, including gamification elements as levels, points, answering questions, rankings, and rewards. In the levels of the game, seven different organs and systems of the human body are simulated, it can vividly show the way HIV invades the human body and its performance if infected with HIV. This can not only improve the fun of the game, but also popularize the process of HIV invading the human body, which may increase users’ willingness to play the game and prevent AIDS.

Four arms were designed in our research, including two intervention arms and two control arms. Participants in the two intervention groups will receive AIDS Fighter · Health Defense, one of which will strictly control the time spent in the game and provides incentives to increase motivation to use the game; Another group will receive AIDS Fighter · Health Defense, but without time limitation or incentives; One of the two control groups is classroom teaching and the other is autonomous learning. By comparing the intervention groups with the control groups, it can be found whether AIDS Fighter · Health Defense is better than classroom teaching and autonomous learning in improving participants’ AIDS prevention ability; By comparing the two intervention groups, we can figure out whether AIDS Fighter · Health Defense is attractive, whether players will voluntarily use the game to improve AIDS prevention capabilities. This will determine whether the game can be promoted on a large scale. By comparing the two control groups, we can understand the difference between classroom learning and autonomous learning in improving AIDS prevention capabilities. Such a design could see the differences in the effects of game-based intervention, classroom teaching, and independent learning in AIDS education. And provide evidence for choosing different AIDS education methods.

We hope that the game-based interventions can be widely used in AIDS education in China and other countries. However, some countries are exam-oriented in evaluating the effect of education and there may be some resistance to the promotion and application of the game; parents may worry that their children will be addicted to the game and affect their academic performance [26, 27]. To address this problem, we can perform identity authentication when the player enters the game and prevent minors from being addicted to the game by limiting the online time.

“AIDS Fighter · Health Defense” could be suitable for the public, high-risk groups of AIDS, and HIV-infected people. It could be an auxiliary educational tool for AIDS prevention for the public and high-risk groups, and for HIV-infected people to maintain long-term ART adherence and keep virus suppression. We believe that with the development of this study, we can provide an AIDS education method for China and other countries to improve the ability to prevent AIDS of public and the quality of life of HIV infected.

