**Methods:**

A protocol for conducting a randomized controlled trial to evaluate the “AIDS Fighter · Health Defense”, a game-based AIDS education project aimed at improving the ability of adolescents to prevent AIDS. During the four-week intervention, participants will receive: 1) A virus combat game; 2) Goal setting to eliminate HIV; 3) Questions to be answered to be resurrected in the game; 4) Points ranking; 5) Recognition and Rewards. The primary outcomes include changes in participants’ knowledge, stigma attitude, and risk behaviors attitude related to AIDS after four weeks of intervention. The secondary outcomes are the participants’ AIDS-related risk behaviors three and six months after the intervention.

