### Intervention group: overview

#### AIDS fighter · health defense intervention group 1

Participants will receive the educational game “AIDS Fighter · Health Defense” and will be required to play the game and learn AIDS education essays or videos in the “knowledge corner” at least 5 days a week and 20 min a day. A data management system will be used to monitor the time participants played in the game, and whether they have learned the content in the “knowledge corner”. After four weeks of intervention, the effect of the intervention will be evaluated by using the same questionnaire as applied in the baseline survey.

Participants will be informed that they will be recognized and rewarded after completing daily game tasks and completing four-week follow-up assessments according to the points ranking. The top 20% will receive a “Gold Award” and 50 RMB in cash, the middle 30% will receive a “Silver award” and 50 RMB in cash, and the lowest 50% will receive a “Bronze award” and 20 RMB in cash.

#### AIDS fighter · health defense intervention group 2

Participants will receive “AIDS Fighter · Health Defense”, without limitation in time to play the game or learn the content of the “knowledge corner”, and there are no incentives as recognition or rewards. Participants play this game according to their preference. Four weeks later, the same questionnaires will be used to measure the effect of their use of the game.

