### Control group: overview

#### Control group 1

Participants will receive classroom teaching once a week for 100 min each time. The total time is the same as the time required by the AIDS Fighter · Health Defense intervention group 1. A regular teacher will conduct AIDS prevention classroom education on a fixed day each week and the content of the lecture is consistent with the knowledge in the game.

#### Control group 2

Participants will be added to the QQ chat group (one of the most popular social tools in China), and the same educational resources as the “knowledge corner” in AIDS Fighter · Health Defense will be uploaded to the QQ group. Participants will then be reminded to learn the knowledge by themselves daily. But there are no gamification elements, such as barriers, points ranking, answering questions, rewards, etc.

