### Data management and statistical analysis

All data will be directly recorded in the online database (www.wjx.cn, Ranxing information technology co., Ltd., Changsha, China). The database system automatically saves the data and ensures the safety, integrity and consistency of the data. The web server is hosted in Alibaba Cloud (Alibaba Group, Hangzhou, China) and is protected by a corporate firewall, while a daily backup mechanism can ensure data security. Data has multi-level permission settings and password protection to ensure data security. In statistical analysis, general statistical analysis will be carried out by using standard statistical software and professional statistical software.

Analysis of Variance (ANOVA) will be used to find out whether there have differences between the AIDS Fighter · Health Defense intervention groups and the control groups in AIDS-related knowledge scores and attitude scores after the intervention of four weeks. Repeated Measures ANOVA will be used to see whether there have differences on the incidence of AIDS-related behaviors followed up for three and six months after the intervention in four arms. Intention-to-treat analysis will be used to account for the influence of attrition. The difference was statistically significant when *P* ≤ 0. 05.

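### Only game group 1 earns points-ranked awards and cash, yet it counts towards the conclusion that the game itself beats classroom teaching and self-study, so an incentive effect could be reported as a game effect

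*Protocol article*

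**What the plan says.** All references are to the protocol article.

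- **Game group 1** (Intervention group: overview) must use the game and its learning material for a set time. Participants are told that "they will be recognized and rewarded after completing daily game tasks and completing four-week follow-up assessments according to the points ranking". The top 20% and the next 30% each receive 50 RMB with a gold or silver award, and "the lowest 50% will receive a “Bronze award” and 20 RMB in cash".
- **Game group 2** (same section) receives the game with no required time, and "there are no incentives as recognition or rewards".
- **Controls** (Control group: overview). No ranked award is described for control group 1, the classroom arm. Control group 2 gets the learning material through a chat group: "But there are no gamification elements, such as barriers, points ranking, answering questions, rewards, etc".
- **All arms** (Recruitment) receive a flat 30 RMB on completion, which does not depend on performance.
- **Comparison.** The second hypothesis in Study design sets the game groups against the control groups. The ANOVA in Data management and statistical analysis looks for "differences between the AIDS Fighter · Health Defense intervention groups and the control groups in AIDS-related knowledge scores and attitude scores".
- **Conclusion drawn.** The Discussion states that from this comparison "it can be found whether AIDS Fighter · Health Defense is better than classroom teaching and autonomous learning".

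The article is not consistent on what the game includes. The abstract lists "5) Recognition and Rewards" among the things participants will receive, Control group: overview counts rewards as gamification, and the Discussion names rewards among the game's elements. But group 2 gets the game without them, and a later paragraph of the Discussion describes incentives as something one arm provides to raise motivation to use the game.

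**The concern.** The conclusion is about the game. One of the two arms that carry it differs from the controls by the game and also by a ranked cash incentive.

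The incentive is not remote from the outcome. Under Points and rankings, points come partly from reading articles and watching videos in the knowledge corner. Control group 2 receives those same resources, and the classroom lectures are meant to match the game's content. Group 1 is therefore partly paid to study material that the controls study without ranked pay, and AIDS knowledge is a primary outcome.

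If group 1 does better for that reason, the result could be published as evidence for the game format. A school that adopted the game without cash awards might not see the gain.

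**Working it through.** **1. The plan's own sample size.** Recruitment gives 131 per group at 80% power, 10% attrition, 145 per group and 580 in total.

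- 131 × 1.10 = 144.1, rounded up to 145; 131 / 0.90 = 145.6, rounded up to 146. The stated 145 is reproduced to within one participant.
- 4 × 145 = 580.
- No effect size or SD is given, so 131 cannot be rebuilt. At two-sided 0.05 (assumed, since sidedness is not stated) and 80% power it implies a detectable pairwise difference of (1.960 + 0.842) × √(2/131) = 0.346 SD.

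**2. What differs between the arms.**

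| Arm | Required contact time | Ranked awards and cash |
|---|---|---|
| Game group 1 | 5 days × 20 min × 4 weeks = 400 min | Yes |
| Game group 2 | None set | No |
| Control 1 (classroom) | 4 × 100 min = 400 min | None described |
| Control 2 (chat group) | None set; daily reminders | No |

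If everyone in group 1 qualifies, the mean award is 0.2 × 50 + 0.3 × 50 + 0.5 × 20 = 35 RMB. With the flat 30 RMB, group 1 averages 65 RMB against 30 RMB in the other arms. Gold and silver pay the same, so rank changes the cash by 30 RMB, between the upper and lower halves.

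Group 1 against classroom is matched on time but not on incentive. Group 2 against classroom is matched on incentive but not on time. Group 1 against group 2 differs in both, so it cannot isolate the cash.

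**3. Illustration of what the incentive could do.** Assumptions: the game adds nothing over either control; incentives alone add c SD in group 1 and nothing elsewhere; 131 analysed per arm; two-sided 0.05; normal approximation. The documents give no value for c.

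- Pooled game arms against pooled controls: the shift is c/2 and the standard error is √(2/262) = 0.0874.
- Group 1 against one control: the shift is c and the standard error is √(2/131) = 0.1236.
- Chance of significance = Φ(shift/SE − 1.96) + Φ(−shift/SE − 1.96).

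| Assumed c (SD) | Pooled, 262 v 262 | Group 1 v one control, 131 v 131 | Group 2 v a control |
|---|---|---|---|
| 0.2 | 21% | 37% | 5% |
| 0.3 | 40% | 68% | 5% |
| 0.4 | 63% | 90% | 5% |
| 0.5 | 82% | 98% | 5% |

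Worked case, c = 0.3, pooled: 0.15 / 0.0874 = 1.717, and Φ(1.717 − 1.960) = Φ(−0.243) = 0.404; the other tail is negligible.

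Splitting the arms does not remove the problem from group 1, whose contrasts then carry the whole of c instead of half. It does leave the group 2 contrasts free of it.

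**4. Precision.** Detectable difference at 80% power: 2.802 × √(2/131) = 0.35 SD for one arm against one arm, and 2.802 × √(2/262) = 0.245, about 0.25 SD, if arms were pooled in pairs.

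**The case against.** The authors have a reasonable case on several points.

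- **The design anticipates the issue.** Group 2 is an incentive-free game arm, and the article says openly that one arm has incentives and the other does not. This stands, and it is why the remedy needs no extra participants. It does not supply the missing caveat where the conclusion is drawn. The hypothesis of no difference between the two game groups does not help either: a non-significant result would not show that incentives do nothing.
- **Pooling is not stated.** The ANOVA sentence speaks of groups in the plural, and the follow-up analysis refers to four arms. A four-arm analysis with pairwise contrasts fits the text. This stands, so the pooled figures apply to one reading only. On the other reading, group 1's own contrasts with the controls still include the incentive.
- **Rewards may be part of the tested package.** Three places in the article support this, and group 1 against a control is then a legitimate comparison of a package. But the conclusion names the game, and group 2 is described as receiving that same game without rewards. The two accounts have to be reconciled.
- **Required use is not a nuisance.** Required playing time is exposure to the game, so a benefit from it should not be counted as spurious. This is right, and c above stands for incentives alone.

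A reader might go further and infer that the game claim must rest on group 2 against classroom as the one clean test. The documents do not support that: classroom time was matched to group 1, so that contrast exchanges the incentive difference for an exposure difference. A reader might also propose paying the controls on the same scale. The awards follow game points, which the controls do not earn, and control group 2 is designed without rewards.

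**Conclusion.** The concern holds as a mismatch between comparison and conclusion. Group 1 alone has ranked awards and cash, it is included in the comparison behind the claim about the game, and nothing in the article limits that claim. The conflicting descriptions of whether rewards belong to the game make the claim harder to interpret.

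The size is unknown. The 21% to 82% range depends on an assumed incentive effect of 0.2 to 0.5 SD, no game effect at all, and pooled arms. It shows that an incentive effect could produce a positive result. It does not estimate how likely that is, and it should not be read as evidence that the cash has such an effect. The comparison remains estimable and group 1 against classroom remains informative; what is unsupported is attributing the result to the game alone. The change should be made, and it concerns reporting and wording, not the conduct of the trial.

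**What to change.** 1. In Data management and statistical analysis and in the Discussion, report each game group separately against each control group.
2. Describe group 1 contrasts as game plus required use plus ranked cash awards: time-matched to classroom, not incentive-matched.
3. Describe group 2 contrasts as the game as freely used, without incentives: incentive-matched, but not time-matched to classroom.
4. Do not attribute superiority to the game alone unless the group 2 contrasts support it.
5. Correct the abstract to say that recognition and rewards apply to group 1 only, and bring the other descriptions of rewards into line with the description of group 2.

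The cost is mostly wording, with no change in sample size. The claim about the game without incentives would rest on 131 against 131 per contrast, with about 0.35 SD detectable at 80% power instead of 0.25 SD under pooling; 131 is the per-group number the article already plans. A null result for group 2 against classroom could reflect low use and not an ineffective game, and should be reported with that caution. The usage times that the game system already records would help to interpret it.

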## Data Availability

The data collected in this study will be published in papers after the study is completed. And the original data will be uploaded to the Chinese Clinical Trial Registration Center, which can be found by searching for the registration number of this study.

## Abbreviations

AIDS: Acquired Immune Deficiency Syndrome
HIV: Human Immunodeficiency Virus
IMB Skills Model: Information-Motivation-Behavioral skills model
PrEP: Pre-exposure Prophylaxis
CVI: Content Validity Index
I-CVI: the Item-level CVI
S-CVI: the Scale-level CVI
ANOVA: Analysis of Variance
